## Abstract

**Background:**

Many patients with anxiety or depressive disorders achieve no remission of their symptoms after evidence-based treatment algorithms. They develop a chronic course of the disorder. Current care for these patients usually consists of long-term supportive contacts with a community psychiatric nurse and pharmacological management by a psychiatrist. Data on the effectiveness of these treatments is lacking. A psychosocial rehabilitation approach, where self-management is an increasingly important part, could be more suitable. It focuses on the restoration of functioning and enhancement of patients’ autonomy and responsibility. Treatment with this focus, followed by referral to primary care, may be more (cost-)effective.

**Methods:**

A multicenter randomized controlled trial is designed for twelve participating specialized outpatient mental health services in the Netherlands. Patients with chronic and treatment resistant anxiety or depressive disorders, currently receiving supportive care in specialized outpatient mental health care, are asked to participate. After inclusion, patients receive the baseline questionnaire and are randomized to the intervention group or the usual care control group. The intervention focuses on rehabilitation and self-management and is provided by a trained community psychiatric nurse, followed by referral to primary care. Measurements take place at 6, 12, and 18 months after baseline. This study evaluates both the effectiveness (on quality of life, symptom severity, and empowerment), and cost-effectiveness of the intervention compared to usual care. In addition, a questionnaire is designed to get insight in which self-management strategies patients use to manage their disorder, and in the experiences of patients with the change of care setting.

**Discussion:**

In this study we evaluate the effectiveness and cost-effectiveness of a self-management intervention for patients with chronic and treatment resistant anxiety or depressive disorders in specialized outpatient mental health care. The results of this study may provide a first ‘proof-of-concept’ in this under-researched but important field, and might be relevant for a large group of patients in the context of a transition of the Dutch health care system.

**Trial registration:**

Netherlands Trial Register: NTR3335, registered 7 March 2012.

## Background

Anxiety and depressive disorders are among the most common mental disorders both worldwide and in the Netherlands. International data (the Netherlands and other developed countries) of the lifetime prevalence of these disorders are similar to each other. According to results from NEMESIS-2 (Netherlands Mental Health Survey and Incidence Study-2), the lifetime prevalence of anxiety disorders is 19.6 %, and 18.7 % for major depressive disorder [1, 2]. Also in specialized outpatient mental health care, anxiety and depressive disorders are common: 22.2 % of outpatients have an anxiety disorder and 37.2 % a depressive disorder [2].

A substantial part of patients in specialized outpatient mental health care achieve no remission of their symptoms after treatment that is provided in accordance with the (inter-)national multidisciplinary guidelines [3–5]. Their disorder seems treatment-resistant [6] and they suffer from a chronic course, with an estimated 41.9 % chronicity for anxiety disorders and 24.5 % for depressive disorders [7]. While anxiety disorders may be considered as chronic disorders in itself [8], a depressive disorder is defined as chronic when a depressive episode lasts more than two years [9]. The comorbidity between anxiety and depressive disorders is high (33–54 %) [10–12] and increases with a longer duration of symptoms. Comorbidity, in turn, increases the risk of treatment resistance and chronicity [13, 14]. Chronic and treatment resistant anxiety or depressive disorders are associated with more intense suffering, increased risk of suicide, and poorer social functioning [15, 16].

Care as usual (CAU) for patients with chronic and treatment resistant anxiety or depressive disorders usually consists of long-term supportive contacts with a key clinician, which is regularly a community psychiatric nurse, and pharmacological management by a psychiatrist. This CAU often has no clear purpose, and lacks treatment evaluation. Data on the effectiveness is lacking [17]. Nevertheless, termination of treatment is not considered to be an option due to the persistent symptoms, the level of suffering, and the absence of other treatment options. A psychosocial rehabilitation approach, focused on specific goals, could be more suitable [18, 19]. However, there is no research on feasibility and effectiveness of rehabilitation approaches for anxiety and depressive disorders in specialized outpatient mental health care.

In the development of such an approach for patients with chronic and treatment resistant anxiety or depressive disorders, self-management is an increasingly important element. Self-management for long-term health problems focuses on the restoration of functioning and enhancement of patients’ autonomy and responsibility. Self-management strategies are for instance: symptom management, enacting problem-solving strategies, and implementing learning plans [20]. We do not yet know much about the self-management strategies used by patients with chronic and treatment resistant anxiety or depressive disorders.

For patients with chronic and treatment resistant anxiety or depressive disorders in specialized outpatient mental health care the intervention, ZemCAD (English SemCAD; Self-management for Chronic Anxiety and Depression) was developed, in order to offer them a different perspective. This is also consistent with the transition of the Dutch health care system where the aim is to refer chronic patients to less intensive levels of care when possible. The focus in this study is on the transition from specialized outpatient mental health care to primary care. ZemCAD, the experimental treatment, offers treatment focused on rehabilitation and self-management, provided by a trained professional (a community psychiatric nurse, and in some cases a psychologist), followed by referral to primary care. Liaison consultation with specialized mental health care is an option if required. We compare the intervention to CAU.

The objectives of this study are:To assess the cost-effectiveness of ZemCAD compared to CAUTo evaluate the effectiveness of ZemCAD compared to CAU with regard to quality of life, symptom severity, and empowermentTo get insight in the self-management strategies that patients use to manage their anxiety or depressive disorder;To review the experiences of patients with a change of care setting.

Our hypothesis is that ZemCAD is more cost-effective than CAU. We expect that ZemCAD has outcomes just as good and not inferior to CAU with regard to quality of life, symptom reduction, and empowerment.

## Methods/Design

### Design

In a multicenter randomized controlled trial, with randomization at the level of patients in two parallel groups, the protocolized ZemCAD intervention versus care as usual is studied across twelve participating specialized outpatient mental health care services in the Netherlands. Assessments are at baseline, 6, 12 and 18 months and assessors are blind to randomization status.

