### Recruitment and randomization

Patients that are eligible for participating in the ZemCAD study according to the inclusion and exclusion criteria are asked to participate by their community psychiatric nurse. This nurse informs the patient about the study and provides an information letter to take home. If the patient is interested and consents to participate, the signed informed consent is sent to the coordinating research centre. To check the inclusion and exclusion criteria formally, the current DSM-IV disorders present in the patient were diagnosed with the Mini-International Neuropsychiatric Interview (MINI interview) in the mental health service that provides the treatment of the patient. The MINI is a well-validated semi-structured diagnostic interview used to establish psychiatric disorders according to the DSM-IV [22]. After inclusion, patients receive the baseline questionnaire. Patients and community psychiatric nurses are blind to the patient’s condition until they have completed the baseline questionnaire. Then the patient is allocated to ZemCAD or CAU, using a randomization schedule designed by an independent statistician. To evenly distribute ZemCAD/CAU across community psychiatric nurses, block randomization (block size of four) of patients is used. Questionnaires are completed over the internet. If a patient has no access to the internet, the questionnaires are completed on paper. Patients are informed that participation in the study is voluntary and that they can withdraw from the study at any time. An overview of the study design and patient flow is provided in Fig. 1.

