Patients receiving ZemCAD are allocated to a new and trained professional. This clearly marks the transition from CAU to ZemCAD for both patient and professional. The training of the participating professionals in ZemCAD consists of a two-day course. A prerequisite is that the professionals study the intervention in advance. The two-day course is provided by an expert and trainer in cognitive behavioural therapy and motivational skills for anxiety and depressive disorders. The training combines self-study, lectures, assignments, and group discussions. During the study, three additional booster sessions were given. In addition, in each mental health service monthly booster sessions for the professionals were scheduled.

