### Measurements

At baseline demographics are measured. Measurements take place 6, 12, and 18 months after baseline. Quality of life is measured with the World Health Organization Quality of Life instrument, Brief version (WHOQOL-BREF) [25, 26]. The WHOQOL-BREF measures the overall quality of life in four different areas: physical health, psychological health, social relationships and environment. Anxiety symptoms are measured with the Beck Anxiety Inventory (BAI) [27], a validated self-rated questionnaire to assess the severity of anxiety symptoms. Depression severity is measured with the Patient Health Questionnaire (PHQ-9) [28, 29], a validated self-rated questionnaire to assess the severity of depression symptoms. Empowerment is assessed using the Dutch Empowerment Scale (Nederlandse Empowerment Vragenlijst) [30]. Contacts with health care professionals, medical costs, and productivity costs are measured with the Trimbos and Institute of Medical Technology Assessment questionnaire for costs associated with psychiatric illness (TiC-P) [31]. Using this self-completion questionnaire, direct and indirect costs of health care utilization of patients can be assessed. In addition, the EuroQoL (EQ-5D) [32] is used to compute Quality Adjusted Life Years (QALYs) gained, to be used in the cost-utility analysis.

To get insight in self-management strategies used by patients with chronic and treatment resistant anxiety or depressive disorders, and experiences of patients with a change of care setting, a questionnaire is designed. We do this by organizing focus groups, and use concept mapping [33] for processing the data. The questionnaire is administered during the ZemCAD trial, to all participants, in both conditions. An overview of measurements is provided in Table 1.

**Table 1 Tab1:** Overview of measurements

	Baseline	6 months	12 months	18 months
Demographics	x			
Clinical depression/anxiety (MINI)	x			
Quality of life (WHOQOL-BREF)	x	x	x	x
Anxiety (BAI)	x	x	x	x
Depression (PHQ-9)	x	x	x	x
Empowerment (Dutch Empowerment Scale)	x	x	x	x
Health care costs (TiC-P)	x	x	x	x
Health care costs (EQ-5D)	x	x	x	x
Questionnaire about self-management strategies and experiences with a change of care setting				x

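### The Design section says assessors are blind through 18 months, but every follow-up measure is completed by patients who know their arm

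*Protocol article*

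**What the plan says.** The Design section of the Protocol article attaches blinding to the whole assessment schedule in one sentence: "Assessments are at baseline, 6, 12 and 18 months and assessors are blind to randomization status". It does not say who the assessors are.

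Other sections describe how the data are obtained:

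- **Who knows the allocation.** Under Recruitment and randomization, patients and "community psychiatric nurses are blind to the patient’s condition until they have completed the baseline questionnaire"; allocation follows. Under Intervention, ZemCAD patients move to a new, trained professional, and "This clearly marks the transition from CAU to ZemCAD for both patient and professional".
- **How questionnaires are collected.** "Questionnaires are completed over the internet", with paper for patients who have no internet access (Recruitment and randomization).
- **What the instruments are.** Under Measurements, the BAI is "a validated self-rated questionnaire to assess the severity of anxiety symptoms" and the PHQ-9 is "a validated self-rated questionnaire to assess the severity of depression symptoms". For the TiC-P: "Using this self-completion questionnaire, direct and indirect costs of health care utilization of patients can be assessed". The EQ-5D "is used to compute Quality Adjusted Life Years (QALYs) gained, to be used in the cost-utility analysis".
- **When they are given.** Table 1 marks the MINI at baseline only. It marks the WHOQOL-BREF, BAI, PHQ-9, Dutch Empowerment Scale, TiC-P and EQ-5D at baseline and at 6, 12 and 18 months, and the self-management questionnaire at 18 months.

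**The concern.** Saying that assessors are blind at follow-up normally means that the person who rates the outcome does not know the treatment arm. Here the person who rates the outcome is the patient, and the patient knows. If no other rater exists, the sentence describes a property that the design lacks for every compared outcome.

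This bears on the trial's main question. The Sample size section says the main hypothesis is health-economic. Its two inputs, QALYs from the EQ-5D and costs from the TiC-P, both come from patients who know whether they were moved to a new programme and on to primary care or stayed with specialised care. Reports could shift either way: enthusiasm for a new programme, or disappointment at losing specialist contact.

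Nothing else in the article deals with such a shift. The bootstrap under Economic evaluation describes sampling uncertainty, and a systematic reporting difference would move the whole bootstrap distribution. The planned sensitivity analyses concern the main cost drivers. The Discussion does not mention blinding or self-report. A reader who relies on the Design sentence could take outcome assessment to be blinded.

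**Working it through.** The article attaches no figure to the blinding statement, and its sample-size figures do not enter, so there is nothing to reproduce numerically. The check sorts each row of Table 1 by who supplies the answer, when, and whether that person knows the arm.

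**Step 1: when blinding ends.** The order under Recruitment and randomization is consent, MINI to check eligibility, inclusion, baseline questionnaire, allocation. Patients and nurses are blind only up to the baseline questionnaire. All assessments at 6, 12 and 18 months come later.

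**Step 2: who rates each measure.**

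| Measure (Table 1) | After randomisation | Who supplies the answer | Basis | Knows the arm? |
|---|---|---|---|---|
| MINI | none (baseline only) | interview at the treating service | Recruitment and randomization | not yet allocated |
| BAI | 6, 12, 18 months | patient | stated, Measurements | yes |
| PHQ-9 | 6, 12, 18 months | patient | stated, Measurements | yes |
| TiC-P | 6, 12, 18 months | patient | stated, Measurements | yes |
| WHOQOL-BREF | 6, 12, 18 months | patient | inferred from online or paper completion | yes |
| Dutch Empowerment Scale | 6, 12, 18 months | patient | inferred, same basis | yes |
| EQ-5D | 6, 12, 18 months | patient | inferred, same basis | yes |
| Self-management questionnaire | 18 months | patient | inferred, same basis | yes |

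Demographics, the remaining row, are recorded at baseline only.

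**Step 3: count.**

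- Measures taken after randomisation: 6 comparative instruments + 1 questionnaire = 7.
- Measure-by-visit entries after randomisation: 6 × 3 + 1 = 19.
- Entries for which the article describes a rater other than the patient: 0 of 19, so 0 of 7 measures.
- Measures for which self-completion is stated outright: 3 of 7. Inferred from the collection mode: 4 of 7.

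**Step 4: what the blinding sentence can still be true of.** At baseline no allocation exists, so an interviewer giving the MINI is blind automatically. After baseline, the only other person described as recording anything about the patient is the ZemCAD professional, who fills in a session checklist (Treatment integrity). That person delivers the treatment, and the checklist is not an outcome in Table 1.

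The sentence therefore holds trivially at baseline and has no described referent at 6, 12 or 18 months.

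**The case against.** **The article is open about the design.** It says when patient blinding ends, says that the change of professional marks the transition, and labels key instruments as self-rated. It never claims that patients or nurses stay blind, and it makes no explicit claim about risk of bias. This stands. A reader might infer that the article hides its open-label character or asserts a protection it spells out; the text supports neither. What remains is one sentence that disagrees with those disclosures.

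**Assessors may mean staff who send, collect or enter questionnaires.** The article neither says nor excludes this. If that is the meaning, the sentence should name those staff. Even then, their blinding would not blind the person who answers the questions.

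**A journal article condenses a fuller protocol.** That covers detail left out. It does not cover a positive statement that does not fit the article's own Recruitment, Intervention and Measurements sections.

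**Open-label conduct cannot be avoided.** Agreed. A visible change of professional and care setting cannot be masked, and the design is not at fault.

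**The harm is not quantified.** This also stands. It is tempting to assume a reporting shift and express it as a share of the 0.45 non-inferiority margin. The documents give no size for such a shift, and the Sample size section itself calls that margin uninformative, so the result would carry no meaning for a decision. The direction is unknown as well.

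**Contact counts as a more objective check.** The Treatment integrity section says contacts are monitored, but the Measurements section obtains contacts through the TiC-P, so on the text they are the same self-report. They also differ between arms by design, because ZemCAD has thirteen sessions and a planned referral. They cannot show whether symptom or quality-of-life reports are biased.

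**Conclusion.** The point holds as an incorrect description of the design. The Design section states blinded assessment at all four time points, yet none of the seven follow-up measures has a blinded assessor. This includes the EQ-5D and TiC-P, on which the main cost-effectiveness hypothesis rests.

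The conclusion rests on two readings. First, the WHOQOL-BREF, Dutch Empowerment Scale, EQ-5D and self-management questionnaire are taken to be completed by patients in the same way as the rest of the set. The article implies this but does not state it for each instrument. Second, no undescribed interviewer takes part at follow-up.

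A reader might go further and conclude that the results will be biased by a known amount, or in favour of ZemCAD. The documents give no basis for a size or a direction. Severity is minor to moderate: the correction matters for how the results are read, but no outcome, model or sample size changes.

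**What to change.** **Design section.** Replace the blinding clause with a statement along these lines: *Patients and treating professionals know the allocation once the baseline questionnaire is complete. The MINI is done before allocation. All follow-up outcomes, including the EQ-5D and TiC-P, are self-reported by patients aware of their allocation.* Then name the staff who remain blind, if any, and for which task; if there are none, say so.

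**Discussion.** Add that conclusions on clinical effects, QALYs and costs are open to reporting bias of unknown direction, and that the bootstrap intervals do not cover it.

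**Optional.** Analysing the data with coded arm labels would guard against analyst choices. It does not remove patient reporting bias and should not be presented as doing so.

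**Cost.** A few sentences, with no change to procedures, sample size or models. The drawback is that the stated risk of bias becomes less favourable.

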### Setting/Participants

The twelve participating specialized outpatient mental health care services offer outpatient treatment interventions for anxiety and depressive disorders, in accordance with the (inter)national multidisciplinary guidelines. For patients with chronic and treatment resistant anxiety or depressive disorders, prolonged treatment (supportive contacts with a community psychiatric nurse) is offered. The transition from specialized outpatient mental health care tot primary care is not considered to be an option due to the persistent symptoms.

Inclusion criteria for the study are:▪ patients with anxiety or depressive disorders according to DSM-IV;▪ >18 years;▪ > two years in specialized mental health care;▪ received at least one psychological treatment and at least three medication steps according to the national multidisciplinary guidelines on anxiety and depressive disorders [21];▪ regarded by their clinicians as treatment resistant, meaning that prolonged treatment in a specialized outpatient mental health service according to the professional is unlikely to improve clinical outcomes (e.g. achieve remission);▪ currently having supportive contacts with a community psychiatric nurse.

Exclusion criteria are:▪ life-threatening medical condition;▪ dementia;▪ psychotic disorder;▪ bipolar disorder;▪ alcohol or drugs dependence;▪ not fluent in Dutch language;▪ cognitive problems/indications for low IQ < 80.

### Recruitment and randomization

Patients that are eligible for participating in the ZemCAD study according to the inclusion and exclusion criteria are asked to participate by their community psychiatric nurse. This nurse informs the patient about the study and provides an information letter to take home. If the patient is interested and consents to participate, the signed informed consent is sent to the coordinating research centre. To check the inclusion and exclusion criteria formally, the current DSM-IV disorders present in the patient were diagnosed with the Mini-International Neuropsychiatric Interview (MINI interview) in the mental health service that provides the treatment of the patient. The MINI is a well-validated semi-structured diagnostic interview used to establish psychiatric disorders according to the DSM-IV [22]. After inclusion, patients receive the baseline questionnaire. Patients and community psychiatric nurses are blind to the patient’s condition until they have completed the baseline questionnaire. Then the patient is allocated to ZemCAD or CAU, using a randomization schedule designed by an independent statistician. To evenly distribute ZemCAD/CAU across community psychiatric nurses, block randomization (block size of four) of patients is used. Questionnaires are completed over the internet. If a patient has no access to the internet, the questionnaires are completed on paper. Patients are informed that participation in the study is voluntary and that they can withdraw from the study at any time. An overview of the study design and patient flow is provided in Fig. 1.

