#### Usual care

Patients who are allocated to CAU continue to receive specialized outpatient mental health care, which usually consists of long-term supportive contacts with a community psychiatric nurse, and pharmacological management by a psychiatrist. In most cases patients continue care with their own community psychiatric nurse. Only if the patient allocated to CAU receives treatment from a community psychiatric nurse who is trained to provide the intervention, the patient needs to switch to a different (untrained) community psychiatric nurse. CAU may also involve termination of treatment in specialized outpatient mental health care and referral to primary care. In the ZemCAD intervention, however, this referral is planned and anticipated within the intervention, while in CAU the referral and termination of the treatment only occurs when indicated.

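### A single fixed block size of four, aimed at balance per nurse, could let recruiting nurses predict up to one third of allocations

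*Protocol article*

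**What the plan says.** All references are to the protocol article.

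- Recruitment and randomization gives one block size and its purpose: "To evenly distribute ZemCAD/CAU across community psychiatric nurses, block randomization (block size of four) of patients is used". The schedule comes from an independent statistician.
- The same section says that eligible patients "are asked to participate by their community psychiatric nurse". It also limits the concealment: "Patients and community psychiatric nurses are blind to the patient’s condition until they have completed the baseline questionnaire".
- Setting/Participants makes eligibility depend partly on opinion: patients must be "regarded by their clinicians as treatment resistant".
- The arm then shows in who treats the patient. Intervention: "Patients receiving ZemCAD are allocated to a new and trained professional". Under Usual care, most control patients stay with their own nurse. The exception is a control patient whose nurse has been trained in the intervention; there, "the patient needs to switch to a different (untrained) community psychiatric nurse".
- Design says that assessors are blind. Measurements lists the BAI and PHQ-9 as self-rated, and the TiC-P, used for costs, as self-completed.

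**The concern.** The person who decides whom to invite, and when, also sees how earlier patients of theirs were allocated. With a small block of constant size and balance sought within each nurse's patients, that nurse can count: after two allocations to one arm, the next two must go to the other. Blinding until the baseline questionnaire is complete is no answer to this, because the information comes from previous patients and not from the one being enrolled.

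A nurse who expects a particular arm next can delay or bring forward an invitation, or apply the treatment-resistance judgement more or less strictly. The arms would then differ in prognosis from the start. Adjustment for baseline characteristics, as planned under Statistical analysis, corrects only for what was measured. The outcomes and cost data are reported by patients who know their arm, so blind assessors do not remove the problem, and in any case selection happens before any assessment.

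There is a plausible motive. Setting/Participants says that the services do not regard a move to primary care as an option for these patients because symptoms persist, and ZemCAD ends in that referral.

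**Working it through.** The article gives no figure for predictability, so there is none to reproduce. The calculation below is by enumeration.

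**Inputs.** Block size 4 (Recruitment and randomization). Allocation 2:2 within the block, inferred from the aim of even distribution. Blocks within nurse, implied by "To evenly distribute ZemCAD/CAU across community psychiatric nurses" but not stated as a stratum. 130 to 180 patients (Sample size) and twelve services (Design). The numbers of nurses and of patients per nurse are not given.

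**Complete blocks.** A 2:2 block of four has 6 equally likely sequences. An allocation is certain when one arm's two places are already used.

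| Position in block | Probability that it is certain | Probability that the best guess is right |
|---|---|---|
| 1 | 0 | 1/2 |
| 2 | 0 | 2/3 |
| 3 | 1/3 | 1/3 × 1 + 2/3 × 1/2 = 2/3 |
| 4 | 1 | 1 |

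- Share certain: (0 + 0 + 1/3 + 1)/4 = 33.3%. That is about 43 of 130 or 60 of 180 patients.
- Best guess right: (1/2 + 2/3 + 2/3 + 1)/4 = 70.8%, against 50% under full concealment.

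**Incomplete blocks.** For a nurse with m patients, add the position values over the m places and divide by m. For example, m = 3 gives (0 + 0 + 1/3)/3 = 11.1% certain, and m = 6 gives (4/3)/6 = 22.2%.

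| Patients per nurse | Certain | Best guess right |
|---|---|---|
| 1 | 0% | 50.0% |
| 2 | 0% | 58.3% |
| 3 | 11.1% | 61.1% |
| 4 | 33.3% | 70.8% |
| 5 | 26.7% | 66.7% |
| 6 | 22.2% | 66.7% |
| 7 | 23.8% | 66.7% |
| 8 | 33.3% | 70.8% |
| 11 | 27.3% | 68.2% |
| 15 | 28.9% | 68.9% |

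The ceiling of 33.3% is reached only when the count is a multiple of four.

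**Where this trial may lie.** 130/12 = 10.8 and 180/12 = 15 patients per service. With one recruiting nurse per service, about 27% to 29% of allocations would be certain. With one to three patients per nurse, 0% to 11%. The documents do not say which applies, so the supportable range is 0% to 33.3%.

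**Would a larger fixed block do?** Known fixed blocks of 6 give 25.0% certain and 68.3% correct guesses; blocks of 8 give 20.0% and 66.6%. Enlarging a fixed, known block helps only modestly. Varying the size, not disclosing it, and moving the block from nurse to service address the counting itself.

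**The case against.** The strongest reply is that the ceiling needs three things the article does not state.

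1. *Blocks run within the recruiting nurse.* The article speaks of balance across nurses, never names the nurse as a stratum, and does not separate recruiting from treating nurses. If blocks run by service or over the whole trial, a nurse who sees only their own patients cannot count the sequence.
2. *Nurses know the block size.* Printing it in an article does not show that sites were told during recruitment.
3. *The order can be followed.* Allocation comes after consent, the MINI and the baseline questionnaire, so a nurse with several patients in process may not know which place a given patient will take. A trained nurse's control patients also move to someone else, so leaving or staying does not always identify the arm.

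All three stand as limits on the size of the problem, and they are why no single percentage can be claimed. They do not remove it. Balance within nurse is the natural reading of the stated purpose. A nurse who knows only that the arms are kept even among their own patients can guess the opposite of the first allocation for the second, which in blocks of four is right two times in three. Small caseloads lower predictability, but they also leave blocks incomplete, so the blocking gives only limited balance.

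A reader might infer that one third of allocations in this trial are predictable. The documents do not support that: it is an upper bound under the three conditions and complete blocks. A reader might also infer that the bias favours ZemCAD. The services' reluctance to transfer patients makes that plausible, but a nurse could equally steer demanding patients toward transfer. The direction is not shown.

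It is also fair to say that recruitment may be far advanced: parts of the article are in the past tense, registration was in March 2012 and the cost reference year is 2014. A change to the schedule may therefore affect few patients or none. That is why the fix includes an analysis of patients already randomised.

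**Conclusion.** The concern holds as a conditional weakness of a stated design choice. One fixed, small block is used for balance across nurses while the patient's own nurse recruits and later learns the arm. The safeguards described protect the current allocation but not inference about the next.

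The share of allocations that are certain lies between 0% and 33.3%, and the best guess is right between 50% and 70.8% of the time. The upper ends assume 2:2 blocks within nurse, a known or inferred size, an order the nurse can follow, and complete blocks. Nothing in the article shows that selection occurred, and any resulting bias in outcomes or costs could go either way. It is worth correcting because the remedy is cheap and later covariate adjustment cannot fully repair selection on unmeasured prognosis.

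**What to change.** **Any remaining allocations.** Randomise centrally within mental health service, not within nurse, using randomly varying block sizes that are not disclosed to the services. This needs a new list from the independent statistician and a short amendment. The cost is slightly looser balance per nurse.

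**Patients already randomised.** State the unit within which blocks ran. Then add a sensitivity analysis that excludes, or adjusts for, allocations that were certain from the preceding sequence in their block. It needs only the existing schedule and allocation order.

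Report it as supportive only. Exclusion could remove up to about 43 of 130 patients (leaving 87) or 60 of 180 (leaving 120), and the Sample size section already calls the non-inferiority margin at 130 uninformative. It also leaves in allocations that could be guessed without being certain, so agreement with the main result would be reassuring but would not prove that no selection took place.
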